### Screening interviews

Orientation Memory Concentration Test (OMC;[116]). The OMC is a well-validated, brief test of mental status.

Diagnostic Interview for Anxiety, Mood, and OCD and Related Neuropsychiatric Disorders (DIAMOND; [78]). The DIAMOND is a brief structured diagnostic interview for major psychiatric disorders that has shown strong validity and reliability in comparison with other structured diagnostic interviews [78]. We will use the DIAMOND to document bipolar I or bipolar II disorder diagnoses to assess lifetime or current episodes of major depressive disorder and to ensure that we are excluding those with eating disorders (anorexia, bulimia, binge eating disorder or) at any time since age 18. Those whose symptoms on the DIAMOND are consistent with other specified eating or feeding disorders will also be excluded (e.g., repetitive binging or purging that does not meet the frequency or duration criteria). For those with scores above the threshold on the AUDIT (≥ 8) or DUDIT (≥ 6 for men; ≥ 2 for women and nonbinary individuals), we will administer the alcohol use disorder and/or substance use disorder modules as appropriate to consider exclusion criteria. For those who endorse any symptoms of psychosis on the DIAMOND-self report, we will complete the psychosis module of the DIAMOND.

Columbia Suicide Severity Rating Scale (C-SSRS; [75]). The C-SSRS is a brief, commonly used scale designed to cover suicidal ideation and behavior. Moreover, the use of other measures of suicide risk has been well validated. We will assess suicidal ideation, intent, plan and means in the past 2 weeks and lifetime history of suicide attempt using the screening version of the C-SSRS.

Structured Clinical Interview for Sleep Disorders—Revised (SCISD-R; [86]). The SCISD-R is a semi-structured clinical interview used to assess common sleep disorders. We will use the SCISD-R to assess hypersomnolence disorder and circadian sleep–wake disorders.

## Outcome measures

### Mood assessments

Our primary measures of mood will be interview-based assessments. We will include self-reported measures of mood in addition, as these allow for more frequent and affordable assessments. We will enrich our understanding of the temporal dynamics of change in these processes with our daily measures of mood (EMA), which will be gathered at baseline and at the midpoint of intervention. For comparison with the findings of other studies, we will also gather the Clinical Global Impression (CGI) and Patient Global Impression (PGI) indices. Our primary outcome measures will be interview-based measures of mood symptoms: the MADRS, YMRS, and LIFE score.

Montgomery-Asberg Depression Rating Scale (MADRS;[117]). The MADRS is a brief, widely used, psychometrically sound measure designed to briefly assess the severity of depressive symptoms. It provides standardized probes and behavioral anchors and attains high interrater reliability across studies of unipolar and bipolar disorder.

Young Mania Rating Scale (YMRS;[91]). The YMRS is one of the most frequently used rating scales for assessing the severity of manic symptoms. Each of the 11 items covers the severity of a core symptom of mania. The ratings reflect participant responses to the interview, coupled with clinician observation.

Longitudinal Interval Follow-Up Evaluation (LIFE; [76, 118]). We will use the LIFE to gather variations in manic mood states across the period between assessments to potentially enrich our ability to “catch” small changes between follow-ups. The LIFE will include probes for rapidly cycling symptoms [115].

We will also include the Wellcome Trust recommended self-report measures for depression and mania, the Patient Health Questionnaire (PMQ-9 for mania and PHQ-9 for depression; [94, 95]. Both are brief scales that have been shown to have high internal consistency and to be sensitive to treatment effects.

### EMA of emotion states

We will supplement our gold standard symptom severity interviews with ecological momentary assessment (EMA) probes of emotion states. An EMA has the advantage of providing a potentially more sensitive indicator of early shifts in mood variability [119]. Participants will be sent 5 surveys per day on their smartphones. Participants will be randomly assigned to one of four schedules (adapted to their designated time zone). These schedules allow for three hours between the final survey of the day and their usual bedtime. Surveys will be quasi-randomized during those hours, spaced on average 135 min apart. Participants will have up to 80 min to respond to each survey and will receive one reminder if they do not respond within the first 40 min.

In our EMA, we will use the Mood Zoom probes, which have been validated in BD [120], with additional probes for sleepiness, hyperfocus, and feeling inspired using a parallel format. Our core index derived from dimension reduction of the emotion probes above is the mean variability in daily negative affect (mean square of successive difference). As a secondary test of proposed mechanisms, we will also assess whether TRE, as a circadian intervention, leads to decreased evening levels of arousal (using factor scores). As a secondary outcome, we predict that both indices will decline more from baseline to the intervention midpoint in the TRE condition than in the Mediterranean diet condition and that this level of decrease will predict greater change in symptom severity and quality of life.

### Quality of life

We will use the Brief Quality of Life in Bipolar Disorder (QoL.BD) questionnaire as our index of quality of life [121]. QoL. BD was designed to capture a full spectrum of relevant domains for individuals with BD (physical, sleep, mood, cognition, leisure, social, spirituality, finance, household, self-esteem, independence, and identity) and to be sensitive and pragmatic for repeated assessments in the context of treatment. The measure was developed based on previously available measures, with consultation from consumers and international experts in BD. It showed strong internal consistency and correlations with objective measures of functioning [122]. This short version is based on factor-analytic methods, has been validated for online use, and has been shown to be sensitive to change in two RCTs [123, 124].

## Secondary outcome measures

In addition to the secondary mood outcomes noted above, we will gather data to assess several other secondary outcomes.

Rey Auditory Verbal Learning Test (RAVLT;[92, 93, 125]). We will administer the RAVLT to assess cognitive benefits of both interventions, given that both interventions are expected to improve inflammation [126–131] and that inflammation has been shown to be related to cognitive performance for those with BD [132–134]. This test has been shown to be sensitive to cognitive deficits associated with BD, even during euthymic periods [135, 136]. We will use the short form that has been adopted by the NIMH Toolkit.

To harmonize our findings with those of other Wellcome Trust grants, we included three measures as secondary outcome measures: the World Health Organization Disability Assessment Schedule 2.0—Brief (WHODAS 2.0-Brief; [99])**,** GAD-7 [137] and the panic, social anxiety and PTSD subscales of the Rapid Measurement Toolkit (RMT20; [138]). The WHODAS 2.0-Brief is a 12-item survey that assesses overall role functioning across major life domains. The GAD-7 is a commonly used measure of generalized anxiety symptoms. The RMT20 is a brief screening tool developed using IRT analyses and well validated against clinical diagnoses [138].

### Intervention acceptability probes

We will use acceptability probes previously validated in the ORBIT clinical trial for BD [109), rated on a scale from “Strongly Disagree” to “Strongly Agree”. We will supplement these with specific questions to assess whether individuals perceive that their mania, depression, sleep, or quality of life improve or worsen following the intervention. Our primary index of acceptability will be the percentage of individuals who endorse that they agree or strongly agree that they would recommend the food plan to a friend. Ratings of “agree” or “strongly agree” for each item will be considered acceptable. As a further check of potential negative outcomes, participants will be asked open-ended queries regarding problems associated with the intervention. For transparency, we will present a table with the full set of items for evaluating acceptability.

### Treatment adherence

#### Food intake schedules

 Food intake schedules, including adherence to the planned schedule, will be assessed using reminders sent by cellphone. The logs are designed to be simple to complete and to lower burden by allowing participants to take a photo of their food or to briefly note the food without the burdens of inputting portion size or calories. Participants can complete their diet log in real time, although missed entries can be added retroactively. Researchers have full access to the data, which will never be shared with commercial entities. This type of photo logging of food by cellphone logs has been validated in several ways [139]. First, compared with reports from questionnaires covering longer time periods, the number of ingestion events captured through a cellphone app is comparable or surpasses the number of meal records found in NHANES 24-h recall data. Second, the caloric content reported surpasses calculated energy requirements. Third, logs capture a significantly longer duration of eating windows per day and more variability in eating rhythms (including weekend delays in breakfast).

Adherence will be scored based on the time of their first and final caloric consumption each day. We will use well-validated metrics for scoring this based on previous research with TRE, in which we will define the time interval that contains 95% of intake events. This approach is less skewed by occasional nonreporting of events or infrequent deviations from the diet and thus provides a more robust and reliable approach to measuring change [140]. Following standards in other US and European studies of TRE, we will focus on days in which participants adequately logged (e.g., entered at least two intake events, covering at least a 5-h window) and will calculate the percentage of days in which individuals met the eating window goal. High adherence will be defined as meeting this standard on at least 78% of the days logged. As supplemental data, we will report the percentage of days logged and the percentage of days in which individuals logged adequately and followed the planned window.

#### Mediterranean diet adherence

Adherence to the Mediterranean diet will be assessed using a food frequency questionnaire (FFQ) gathered at baseline and at the midpoint of intervention. We designed FFQ probes to score the Alternate Mediterranean Diet score, which is an updated version of the original Mediterranean Diet score to integrate median intake levels by sex [141, 142]. Within this scoring system, participants receive 1 point for the consumption of > median amounts of vegetables, fruits, legumes, nuts, whole grains, and fish; for a favorable ratio of monounsaturated to saturated fats; and for lower levels of red or processed meats and for lower alcohol use. These FFQ diaries will be supplemented with coding based on the text or photo food log entries.

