## Secondary hypotheses

To examine the effects of TRE on day/night rhythms, we will assess the following effects on improving sleep hygiene behaviors (Sleep Household Environment and In-Bed Behaviors), sleep quality (Consensus Sleep Diary and Patient-Reported Outcomes Measurement Information Systems (PROMIS) self-ratings), sleep midpoint variability (Munich Chronotype Questionnaire; MCTQ), and regularity of daily routines (Brief Social Rhythm Questionnaire). To provide a more refined index of early changes in emotion, we will assess the effects of TRE on daily emotional lability (as assessed using ecological momentary assessment (EMA)). We expect adherence to both dietary interventions to be related to improvements in verbal memory (short form of the Rey Auditory Verbal Learning Test (RAVLT)). We will conduct exploratory analyses to examine a broader range of secondary outcomes and to test potential moderators.

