Starting on day 5 after baseline, we will gather several daily measures sent by REDCap through text message. Participants will complete the Core Consensus Sleep Diary (Core CSD; [87]) to assess sleep quantity, timing and quality each morning for 10 days until the end of the baseline period. Participants will also complete EMA of 5 prompts per day for 8 days with brief probes to assess mood (detailed below). We will send the CSD and EMA probes on at least 2 free days for each individual (e.g., one Saturday and Sunday). After the 8 days of mood monitoring, participants will be asked to complete day-after food frequency diaries on the final two days of baseline (one free day and one workday) to capture the quantity consumed for each component of the Mediterranean Diet (e.g., fruit, vegetables, whole grains, olive oil).

After at least 3 days of adequate logging, participants will be sent links to schedule the baseline interview (longitudinal interval follow-up evaluation [LIFE]; [76, 88, 89]; Montgomery-Asberg Depression Rating Scale [MADRS]; [90]); Young Mania Rating Scale [YMRS]; [91]; and the short form of the Rey Auditory Verbal Learning Test [RAVLT]; [92, 93]) and will be asked to complete a preintervention baseline battery of online questionnaires for demographic information, symptoms, sleep, and functional information (Patient Mania Questionnaire [PMQ-9]; [94]), Patient Health Questionnaire [PHQ-9]; [95], and Brief Quality of Life in Bipolar Disorder (QoL.BD; [96]), PROMIS Sleep Disturbance and Sleep-Related Impairment [97], Sleep Household Environment and In-Bed Behaviors [98] World Health Organization Disability Assessment Schedule (WHODAS 2.0-Brief; [99]). The participants were also asked to complete measures of potential moderators (Household Food Security Survey [HFSSM]; [100]), Positive Urgency [101], Personality Traits (PID5BF + ; [102]), Risky Families [103], and for women in appropriate age ranges, the Menopause-Specific QoL Sleep [hot-flash] items [104, 105]).

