### Assessments during the intervention and follow-up

Participants will be asked to complete daily food logs using brief text entries and optional photos with a cellphone app throughout the 8-week intervention period. At 6, 9, and 15 months after the end of baseline, participants will log their food (first intake and last intake) for 10 days in the app. Sleep diaries (core CSD) and EMA data will be collected for 8 days at the midpoint of the intervention. For one weekday and one weekend after the EMA ends, all participants will be asked to provide day-after food frequency diaries to be able to code Mediterranean diet adherence. Symptom severity and LIFE interview assessments will be conducted at the midpoint, at the end of the intervention, and at 6, 9, and 15 months after the end of baseline. Self-rated assessments of symptom severity, QoL, and sleep/circadian variables will be conducted at each of those assessments and at 16 weeks post baseline. The secondary outcome and eating disorder measures will be administered postintervention but not at follow-ups.

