### Mediterranean diet

The Mediterranean Diet is a plan for healthy eating based on how people eat and drink in the 16 countries that border the Mediterranean Sea. Individuals will be encouraged to consume vegetables (6 servings/day), fruits (2–4 servings/day), whole grains (daily), legumes (3–4 times per week), nuts (0.5 oz per day), and oily fish (2 servings/week). Participants will be encouraged to choose lean meats and other sources of protein over red meat and processed meats. Sweets (including desserts and refined cereals), alcohol, and wine or alcohol will be labeled extras, and participants will be encouraged to limit their consumption of extras. The Mediterranean diet resource kit provided at the time of randomization will include a list of key foods, a plan for setting feasible goals for change in the first week, an outline for planning grocery shopping, suggestions for following the Mediterranean diet on a budget, healthy snack options, and tips for finding recipes that meet cultural or food allergy guidelines. Interventions will be followed for eight weeks. To match the burden and self-monitoring of the TRE condition, participants in the Mediterranean diet condition will also be asked to log their food intake using the app.

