### Sensitivity analysis of the primary outcome

To corroborate the robustness of the findings, we will conduct analyses restricted to those participants who completed the baseline and postintervention symptom assessments and who also showed at least 80% adherence to the intervention during the last month of the intervention (early weeks are expected to include growth in the ability to follow both food plans). For TRE, we will define the eating window as the time window during which 95% of the eating events (the 2.5% to 97.5% interval) occur, and then calculate the proportion of days in which the person followed the planned time window. For the Mediterranean Diet, adherence will be quantified as a mean score of 6 or higher (roughly the 90th percentile) on the Alternate Mediterranean Diet score for the two days assessed at the midpoint of intervention [146].

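### Mediterranean-diet adherence is cut at a mean score of 6 over two single diary days although fish and legumes have weekly targets, so for participants near the cut-off the classification depends partly on which days were sampled (minor)

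*Protocol article*

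**What the plan says.** - **Targets.** Under Intervention content, the Mediterranean diet section sets daily goals for some foods but includes "legumes (3–4 times per week), nuts (0.5 oz per day), and oily fish (2 servings/week". Fish and legumes are therefore not expected every day.
- **Instrument.** The Mediterranean diet adherence section says: "Adherence to the Mediterranean diet will be assessed using a food frequency questionnaire (FFQ) gathered at baseline and at the midpoint of intervention". What is collected is a diary on two days. At baseline, participants "complete day-after food frequency diaries on the final two days of baseline (one free day and one workday"; at mid-intervention, "For one weekday and one weekend after the EMA ends, all participants will be asked to provide day-after food frequency diaries". Table 2 also lists 2 days at each occasion.
- **Scoring.** In the same section, "participants receive 1 point for the consumption of > median amounts of vegetables, fruits, legumes, nuts, whole grains, and fish", and further points are given "for a favorable ratio of monounsaturated to saturated fats; and for lower levels of red or processed meats and for lower alcohol use". That makes nine components, seven of them other than fish and legumes.
- **Cut-off.** The section Sensitivity analysis of the primary outcome treats Mediterranean-arm participants as adherent at a mean score of 6 or higher "for the two days assessed at the midpoint of intervention".
- **Supplement.** The adherence section adds that coding of the text or photo food logs will supplement the diaries, without saying how. The Food intake schedules section says these logs do not ask for portion size or calories. The cut-off rule does not mention them.

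**The concern.** A point needs intake above a median, and zero intake cannot exceed any median. A food meant to be eaten on two to four days a week can easily be absent from two sampled days even when the weekly target is met. For someone on target, this sampling can only remove points.

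The score decides which Mediterranean-arm participants enter the adherent-only analysis, and it is the adherence measure described for that arm. If status near the cut-off depends on which days were sampled, the adherent subset is partly selected by chance and reported adherence is understated for those participants.

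**Working it through.** **The plan's own figure.** The cut-off of 6 is described as roughly the 90th percentile. No score distribution is given, so this cannot be reproduced. The check takes the cut-off as stated.

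**Inputs.** Fish is eaten on k = 2 days a week, and legumes on k = 3 or 4 (Mediterranean diet section). Two diary days are used, one weekday and one weekend day (Assessments during the intervention and follow-up). There are seven other components (Mediterranean diet adherence).

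**Assumptions, not in the documents.** Servings fall on different days placed at random. Fish days and legume days are independent. A food eaten on a diary day earns its point that day. The other points are earned on both days.

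**Step 1: diary days (of two) on which the food appears.** With C(7,2) = 21, the chance of none is C(7−k,2)/21, of one is k(7−k)/21, and of two is C(k,2)/21.

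| Food | none | one | two |
|---|---|---|---|
| Fish, k = 2 | 10/21 = 48% | 10/21 | 1/21 |
| Legumes, k = 3 | 6/21 = 29% | 12/21 | 3/21 |
| Legumes, k = 4 | 3/21 = 14% | 12/21 | 6/21 |

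The weekday-plus-weekend sampling gives the same values when habit days are random.

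**Step 2: sensitivity of the fish figure to placement.**
- Both fish days on weekdays: 3/5 = 60% see none.
- One weekday and one weekend day: 4/5 × 1/2 = 40%.
- Both weekend days: 0%.
- Both servings on one random day: C(6,2)/21 = 15/21 = 71%.

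**Step 3: both foods together (legumes at 3, then 4 days a week).**
- Both missed: (10×6)/441 = 13.6%; (10×3)/441 = 6.8%.
- At least one missed: 1 − (11×15)/441 = 62.6%; 1 − (11×18)/441 = 55.1%.

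**Step 4: chance of a score of 6 or more.** Let h and g be the numbers of diary days with fish and with legumes. The article does not say how the median thresholds apply to diary days, so both readings are shown. Day by day, the score is (other points) + (h+g)/2. Pooled, it is (other points) + 1 if h > 0, + 1 if g > 0.

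- *6 or 7 other points:* 100% under either reading.
- *5 other points, day by day:* h+g ≥ 2 is needed. At k = 3: 1 − (60+120+60)/441 = 201/441 = 46%. At k = 4: 1 − (30+120+30)/441 = 261/441 = 59%.
- *5 other points, pooled:* at least one food must be seen. 1 − 60/441 = 86%; 1 − 30/441 = 93%.
- *4 other points, day by day:* both foods are needed on both days. (1×3)/441 = 0.7%; (1×6)/441 = 1.4%.
- *4 other points, pooled:* both foods must be seen. 165/441 = 37%; 198/441 = 45%.

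Scored over a full week, the same on-target people would total 5 + 2 = 7 and 4 + 2 = 6, both at or above the cut-off.

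**The case against.** The strongest reply is that full adherers are safe. Someone who earns the vegetable, fruit, whole-grain, nut, meat and alcohol points already has 6 and is classed adherent whatever the diary shows about fish and legumes. This stands. A reader might infer that people who follow the whole plan are often misclassified; the scoring rule does not support that. Those affected hold only 4 or 5 of the other seven points. They are not all poor adherers, however. Someone who meets all six numeric targets but earns none of the meat, alcohol and fat-ratio points has exactly 4.

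The figures also depend on the scoring reading. A mean over two days most naturally suggests scoring each day and averaging, but pooling softens the result considerably. Both readings must be shown. Losing both points is uncommon, at 7–14%.

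The food logs run daily through the intervention and could fill the gap. How they enter the score may be set out in a fuller document. That stands for the general adherence measure, but the cut-off rule as written rests on the two days alone, and the logs carry no portion sizes.

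A reader might also infer that the two-day score weakens the verbal-memory hypothesis in the Secondary hypotheses section ("We expect adherence to both dietary interventions to be related to improvements in verbal memory"). That section names no adherence measure, and nothing in the article ties the two-day score to it, so the link is only an inference.

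**Conclusion.** The point holds as a minor one. The stated rule judges two weekly foods from two single days. In 55–63% of on-target participants at least one of the two foods does not appear. This changes status only for those with 4 or 5 other points. For them the chance of being classed adherent ranges from about 1% to 93%, depending on the other points, the legume frequency and the scoring reading.

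The missed-food percentages do not depend on which medians are used, but they do rest on random, separate eating days. The classification figures also assume that a food eaten on a diary day earns its point. How many participants fall in the affected group cannot be told from the article. The consequence is limited to the adherent-only sensitivity analysis and the reported Mediterranean-diet adherence. The intention-to-treat primary analysis does not use the score.

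**What to change.** In Mediterranean diet adherence and in Sensitivity analysis of the primary outcome, score the fish and legume points from a weekly window. Word those two questionnaire items as intake over the past seven days, at both baseline and midpoint so that the two occasions stay comparable. Use the daily text and photo logs to check the number of fish and legume occasions; without portion sizes they cannot by themselves support a score based on amounts. Keep the two diary days for the other seven components, and state whether those days are scored separately and averaged or pooled.

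Under the assumptions above, a seven-day window reduces the chance of missing an on-target food to 0%. For comparison, four diary days in one week would still miss fish with probability C(5,4)/C(7,4) = 5/35 = 14%.

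The cost is the rewording of two items at two occasions and a simple log check. The downside is that past-week recall is somewhat less exact than day-after recall.
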